## Abstract

**Background:**

Minimal change nephropathy (MCN) is a common cause of nephrotic syndrome in both adults and children. International guidelines recommend treatment with prednisolone 1 mg/kg/day to adults. This dose is derived from an empirically established dose in children, although children generally attain remission faster and relapse more rapidly than adults. Prednisolone is associated with multiple and serious adverse events. Activated vitamin D has been shown to reduce albuminuria in other glomerular renal diseases with a minimum of adverse events. This study tests the hypothesis that a new treatment regimen in MCN combining reduced dose prednisolone and active vitamin D is as efficient in inducing remission and has fewer and less severe adverse events than standard prednisolone. Furthermore, we aim to establish models allowing for more personalized medicine based on assessment of the individual’s prednisolone metabolism.

**Methods:**

A randomised controlled multicentre non-inferior unblinded trial including 96 adult, incident patients with biopsy-proven MCN, albuminuria > 3 g/day, and an estimated glomerular filtration rate (eGFR) > 30 ml/min from renal departments in Denmark. Patients are randomised to standard prednisolone (1 mg/kg/day) or reduced prednisolone (0.5 mg/kg/day) and alfacalcidol (0.5 μg/day). The primary outcome is the rate of remissions after 16 weeks and the time from diagnosis to remission. The study will include a saliva test to characterise prednisolone pharmacokinetics and compare them to genetic variations in specific liver enzymes responsible for prednisolone metabolism.

**Discussion:**

Reducing the prednisolone dose is expected to reduce the number of severe adverse events. This study will examine if reduced prednisolone dose with active vitamin D but without additional immunosuppression is feasible in the treatment of MCN and will reduce the number of adverse events. The findings can potentially change current guidelines for treatment of MCN in adults. Additional outcomes on inter-individual pharmacokinetic and metabolic variations may allow for a more personalised treatment strategy.

**Trial registration:**

EudraCT 2017-001206-16, ClinicalTrials.gov NCT03210688. Registered on June 3, 2017.

## Administrative information

The order of the items has been modified to group similar items (see http://www.equator-network.org/reporting-guidelines/spirit-2013-statement-defining-standard-protocol-items-for-clinical-trials/).

## Introduction

### Background and rationale {6a}

Minimal change nephropathy (MCN) is one of the most common causes of nephrotic syndrome worldwide, and it is the underlying pathology in 10–25% of all cases in adults [1]. The nephrotic syndrome in MCN is characterised by an approximately 100-fold or higher increase in urinary albumin excretion, hypoalbuminemia, oedema, and significantly increased plasma lipids [2, 3]. The pathophysiology of MCN is not fully clarified but may be associated with a dysfunctional interaction between the immune system and the glomerular podocyte, which is essential for maintaining the glomerular filtration barrier. Most studies indicate that T cells are involved, although the effect of CD20 receptor antibody treatment indicates that the B cells also play a role.

MCN only rarely leads to end-stage renal disease. However, studies have shown that MCN is associated with an increased risk of mortality [4], cancer [5], and cardio-vascular events, including thromboembolic disease in both children and adults [6, 7]. It is unknown whether it is the disease or the associated treatment that induces long-term complications.

Currently, the Kidney Disease: Improving Global Outcomes (KDIGO) guidelines recommend a high dose of oral prednisolone (1 mg/kg/day) [8] for treatment of adult patients with MCN for up to 16 weeks, depending on their clinical response [8]. This dose is based on an empirical dose (60 mg/m^2^/day) suggested from studies in children [9]. Children, however, generally attain remission faster than adults with 50% being in remission within 8 days of treatment compared with 2 months to remission in adults [2]. Relapse occurs more rapidly in children than in adults and up to 90% of all children with MCN have at least one relapse [2]. In adults, relapse is seen in 30–70% of cases during tapering or after discontinuation of prednisolone [10–12]. According to guidelines, relapse should be treated with a new course of high-dose prednisolone. Thus, a great number of patients are exposed to a large, cumulative dose of prednisolone.

An older observational study in adult patients with nephrotic syndrome suggested that the time to remission is substantially shorter in patients treated with prednisolone than in untreated patients [13]. A small and underpowered study indicated that in adult MCN remission may be induced just as fast when using a smaller cumulative dose of prednisolone [14], than recommended in the present international guidelines, and with no significant differences in the cumulative numbers of relapse although a trend towards earlier relapse with the low-dose regimen was observed [14]. A systemic review comparing standard high-dose prednisolone to a low dose of prednisolone combined with other immunosuppressants suggested no difference in relapse rates [15].

Treatment with active vitamin D reduces proteinuria in various types of kidney disease [16–19]. Studies in patients with IgA nephropathy [16, 18, 20, 21] show that pharmacological doses of active vitamin D reduce urinary albumin excretion. Thus, clinical observations suggest that treatment with active vitamin D may stabilise the glomerular filtration barrier and thereby reduce albuminuria and provide additional benefit to prednisolone. However, this has never been tested in MCN. Furthermore, patients with nephrotic syndrome have low levels of vitamin D because of increased urinary excretion of vitamin-D-binding protein [22, 23], indicating possibly additional benefits from such treatment.

Treatment with prednisolone is associated with important physical and mental adverse effects, including an increased risk of infections, obesity, diabetes, and hypertension and mental changes, e.g. mood changes, depression, and agitation [24], which collectively constitute a strong argument for reducing the cumulative prednisolone dose. Recently, a Glucocorticoid Toxicity Index [25] has been developed to identify and quantitate prednisolone-related complications. The Index includes changes in body mass index, glucose tolerance, blood pressure, lipid status, bone density, steroid myopathy, skin toxicity, neuropsychiatric toxicity, infections, and adrenal insufficiency, as well as gastrointestinal and ocular disease. The Cushing Quality of life (QoL) questionnaire addresses known problem areas in Cushing and is useful for evaluating patient-reported health-related quality of life and correlates with clinical parameters [26, 27]. Also, the short form (SF) 36 is a well-established patient-reported survey that has been used to determine the health-related QoL in the general population and among different groups of patients, e.g. patients with renal disease [28].

The pharmacokinetics of prednisolone are complex. Prednisolone is protein bound, and its metabolism is influenced by gender and plasma albumin as well as by liver function and genetic variations in the enzymes CYP3A4, CYP3A5, ABCB1, and NR112 [29]. Repetitive samplings of non-stimulated saliva provide a good estimate of prednisolone turnover in healthy people [29] and in children with nephrotic syndrome [30]. This may allow for individualised dosing of prednisolone to reduce adverse events without compromising efficacy.

The aim of this study is to test the hypothesis that a new treatment regimen in MCN combining reduced dose prednisolone and active vitamin D is as efficient in inducing remission and has fewer and less severe adverse events than standard prednisolone. Furthermore, we aim to establish models allowing for more personalized medicine based on assessment of the individual’s prednisolone metabolism.

### Objectives {7}

Based on the potential benefits from reducing cumulative prednisolone dose and the possible positive effects of active vitamin D in nephrotic syndrome, the study will test the following hypothesis:
Treatment of MCN with a reduced dose of prednisolone in combination with active vitamin D is non-inferior to standard dose of prednisolone with respect to rate and time to remission.Treatment of MCN with a reduced dose of prednisolone in combination with active vitamin D reduces the incidence of both the observed and subjective adverse events compared with the standard dose of prednisolone.Patients with MCN and a fast turnover of prednisolone have a lower rate of remission, longer time to remission, and fewer adverse events than patients with a slow turnover of prednisolone.

### Trial design {8}

The trial design is a non-inferior, open-label, randomised, controlled multicentre study including 96 patients with primary, biopsy-proven MCN followed at renal departments in Denmark. The patients are randomised to the following:
Standard prednisolone (1 mg/kg/day, maximum 80 mg/day), orReduced prednisolone (0.5 mg/kg/day) and active vitamin D (alfacalcidol 0.5 μg/day).

When remission is achieved, prednisolone will be taped slowly according to an individual plan (defined by body weight at baseline and the result of randomisation). In both groups, prednisolone will be discontinued 25 weeks after remission. Alfacalcidol will be discontinued at the same time. The patients are followed until first relapse of MCN or for 1 year after remission.

### Eligibility criteria {10}

Inclusion criteria:
MCN verified by kidney biopsyNephrotic syndrome at diagnosis (defined as albuminuria > 3 g/day and hypoalbuminemia by local reference range)Age ≥ 18 years

Exclusion criteria:
Secondary MCN due to, e.g. systemic immune-mediated disease, lymphoma, solid cancer, etc., based on the investigator’s assessment.An episode of nephrotic syndrome within 5 years from inclusion and/or previous treatment with immunosuppressive medication other than prednisoloneActive cancer disease, except from basal cell carcinomaPregnancyeGFR < 30 ml/min/1,73 m^2^ (CKD-EPI)Unable to receive information and/or provide informed consentAllergy or intolerance to prednisolone or alfacalcidol

### Who will take informed consent? {26a}

The local investigator (MD) will provide oral and written information about the study to all eligible patients and ask for consent to participate in the study. If patients agree to participate, they will be required to sign written informed consent.

### Additional consent provisions for collection and use of participant data and biological specimens {26b}

Not applicable.

### Interventions

#### Explanation for the choice of comparators {6b}

The choice of comparator is based on international guidelines (prednisolone 1 mg/kg/day) [8].

#### Intervention description {11a}

Patients will be randomised to either standard treatment with prednisolone 1 mg/kg/day or treatment with prednisolone 0.5 mg/kg/day combined with alfacalcidol 0.5 μg/day. The starting dose will remain unchanged until remission of MCN. After remission, prednisolone will be tapered slowly and discontinued after 25 weeks. All trial sites follow the same tapering regimen. The alfacalcidol dose remains unchanged while the patients receive prednisolone and is discontinued along with prednisolone.

#### Criteria for discontinuing or modifying allocated interventions {11b}

Prednisolone dose in both arms as well as alfacalcidol dose in the experimental arm may be reduced or discontinued if patients develop severe adverse events to these drugs as assessed by the local investigator. If possible, any deviation from the dosing regimen should be discussed with the sponsor prior to modification. Examples of severe adverse events are hypercalcaemia due to alfacalcidol treatment or psychoses, osteoporotic fracture, development of diabetes, or severe infections during high-dose prednisolone treatment.

#### Strategies to improve adherence to interventions {11c}

Prednisolone and alfacalcidol will be provided free of charge to patients from the local renal department. At each visit, the patients will be asked to bring study medication to be counted by the study nurse and registered in an individual medication log to ensure adherence to the medication. If the patients absent from study visits or biological tests, the study nurse will contact them by phone and rearrange visits to ensure adherence to the study protocol.

#### Relevant concomitant care permitted or prohibited during the trial {11d}

During the trial, patients may receive additional treatment for hypertension, hyperlipidaemia, and fluid control as well as prophylaxis targeting osteoporosis, gastric ulcers, and thrombosis according to local guidelines. The patients cannot receive other immunosuppressants or active vitamin D during the trial.

### Provisions for post-trial care {30}

Trial participants are covered by the national standard patient insurance. In case of harms related to the trial participation, patients will be compensated according to the national established guidelines. The local renal departments will be responsible for the post-trial care according to local procedures. Participants in the trial will post-trial be followed at their local nephrologists at the renal departments as traditionally.

### Outcomes {12}

Remission is defined by a urine-protein/creatinine ratio < 0.4 g/g and/or a urine-albumin/creatinine ratio < 0.3 g/g on two consecutive tests.

Relapse is defined as the recurrence of proteinuria, i.e. a urine-protein/creatinine ratio > 0.75 g/g and/or urine-albumin/creatinine ratio > 0.5 g/g in two consecutive tests and a decline in p-albumin of > 3 g/l.

Primary endpoints:
Rate of remissions after 16 weeks.Time from diagnosis to remission.

Secondary endpoints:
Rate of relapse within 1 year after remission.Time from remission to relapse.Rate of adverse events and number of hospital admissions.The associations between genetic variations in liver enzyme genes, the concentration of prednisolone in saliva, and remission or relapse.

Safety endpoints:
Patient survivalAcute kidney injury (AKI stage 2 or 3 as defined by KDIGO [31])Serious infections requiring admissionPersistent hypercalcaemia (> 2 weeks) defined by an elevated plasma-ionised-calcium and not normalising by reducing alfacalcidol dose.Severe adverse effects to prednisolone, e.g. gastrointestinal bleeding and severe depression

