### Sample size {14}

Based on current data, 80% of patients are expected to achieve remission after 16 weeks of standard treatment [8]. It is considered clinically significant if the remission rate in the low prednisolone + alfacalcidol regimen is less than 90% of the standard treatment regime. Using a non-inferior design with 80% power and a P value of = 0.05, we estimate that 43 patients in each group would need to complete the study. To allow for withdrawals, the study will recruit 96 patients. The incidence of adult MCN in Denmark is 7.3/m/year [4], and with all Danish renal departments participating in the trial, the inclusion is expected to be completed within 4 to 5 years.

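### Time to remission, a primary endpoint claimed as non-inferior, is counted from diagnosis rather than randomisation, so time that allocation cannot influence enters the comparison

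*Protocol article*

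**What the plan says.** The Outcomes section {12} of the protocol article lists two primary endpoints: the remission rate after 16 weeks, and "Time from diagnosis to remission". The abstract's Methods paragraph says the same: "The primary outcome is the rate of remissions after 16 weeks and the time from diagnosis to remission". The Objectives section {7} states the hypothesis for both together, namely that the reduced-dose regimen "is non-inferior to standard dose of prednisolone with respect to rate and time to remission".

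Other sections place diagnosis before allocation. Eligibility {10} requires biopsy-verified disease. Patients are then informed and asked for consent {26a}, baseline data are collected before randomisation {17a}, and allocation follows registration in RedCap {16c}. The text sets no maximum interval between diagnosis and randomisation. The participant timeline is a figure that is not available here.

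The Sample size section {14} bases its control rate on time under treatment: "80% of patients are expected to achieve remission after 16 weeks of standard treatment". Its margin, a rate "less than 90% of the standard treatment regime", concerns the remission rate only. No margin or sample size is given for time to remission.

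**The concern.** A randomised comparison is cleanest when the clock starts at the point where the arms begin to differ. Here it starts earlier. The stretch from diagnosis to randomisation has the same expected length in both arms and cannot respond to the allocated regimen, yet it is part of the measured outcome.

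In a superiority trial this would mainly cost power. In this trial the claim is non-inferiority for time to remission. Anything that makes a truly slower regimen look closer to standard therefore works in favour of the claim. Whether that happens, and how strongly, depends on the summary measure used and on how much the delay varies between patients.

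The two primary endpoints also appear to run on different clocks: one on weeks of treatment, the other from diagnosis.

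**Working it through.** **Plan's own figure.** The plan gives no figure for time to remission. Its sample size statement, "we estimate that 43 patients in each group would need to complete the study", rests on the 16-week rate alone and does not depend on the time origin. It is used below only as a group size. (Whether 43 follows from the stated inputs is a separate matter.)

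**1. Equal delay, effect on medians.** Inputs: 80% remission at 16 weeks (Sample size {14}). Assumptions: exponential remission times, a true remission hazard ratio of 0.75, and an equal delay d of 0 to 4 weeks.

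- Control median = 16 × ln 2 / (−ln 0.2) = 6.89 weeks.
- Reduced-dose median = 6.89 / 0.75 = 9.19 weeks.
- Difference = (9.19 + d) − (6.89 + d) = 2.30 weeks for every d.
- Ratio = (9.19 + d) / (6.89 + d).

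| d (weeks) | 0 | 1 | 2 | 3 | 4 |
|---|---|---|---|---|---|
| Ratio of medians | 1.33 | 1.29 | 1.26 | 1.23 | 1.21 |

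The difference is unaffected and the ratio moves toward 1. Medians of 8 and 12 weeks show the same pattern: 12/8 = 1.50, 14/10 = 1.40 with 2 weeks added, 16/12 = 1.33 with 4.

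**2. Equal delay, effect on the hazard ratio.** Cox and log-rank results depend only on the order of the event and censoring times. Adding one constant to every time keeps that order, so the result is identical.

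**3. Delay that varies between patients.** This was simulated with 43 patients per arm and 6,000 runs per scenario. The assumptions were exponential times, a control median of 8 weeks (the Background {6a} gives about 2 months for adults), a true hazard ratio of 0.60, 16 weeks of follow-up from randomisation, and no remission during the delay. The hazard ratio is the log-rank estimate exp(U/V), where U is observed minus expected events and V its variance. False non-inferiority is the share of runs in which U/V − 1.96/√V exceeds ln 0.60, that is, with 0.60 taken as a hypothetical margin at one-sided 2.5%.

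| Delay | HR from randomisation | HR from diagnosis | False non-inferiority, randomisation | False non-inferiority, diagnosis |
|---|---|---|---|---|
| Constant 2 weeks | 0.594 | 0.594 | 2.8% | 2.8% |
| Uniform 0–4 weeks | 0.595 | 0.597 | 2.5% | 2.5% |
| Exponential, mean 2 weeks | 0.592 | 0.597 | 2.5% | 2.5% |
| Exponential, mean 4 weeks | 0.593 | 0.608 | 2.3% | 3.2% |
| Exponential, mean 8 weeks | 0.590 | 0.635 | 2.6% | 4.5% |

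The simulation error of a 2.5% rate is √(0.025 × 0.975 / 6000) = 0.2 percentage points. The rise at a mean of 4 weeks is therefore modest, and the rise at 8 weeks is clear. A separate Cox simulation with a true hazard ratio of 0.75 and a delay that was constant at 2 weeks, uniform over 0–4 weeks or uniform over 0–8 weeks gave estimates of 0.746 to 0.753, essentially no change.

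**The case against.** The strongest reply is that the ordinary analysis of such an endpoint, Cox or log-rank, is barely affected unless the delay is both long and variable. The ratio shrinkage in step 1 belongs to an analysis that the protocol does not name. The delay itself is unknown, and the timeline figure might bear on it. This stands, and it limits the size of the point. It does not justify the origin: the protocol states the origin, gives no reason for it, and in the text shown does not commit to a method that would make it harmless.

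Several stronger readings are tempting but not supported:

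- A reader might infer that the added time dilutes a difference the trial must detect. An equal delay leaves the difference in times unchanged, and a non-inferiority trial has no difference it must detect.
- A reader might infer that the interval is untreated. Eligibility {10} excludes earlier immunosuppressants apart from prednisolone, so this is not established. Nor does the text re-check nephrotic status at randomisation, so a remission-free interval is the simulation's assumption, not a documented fact.
- A reader might infer that the clocks are known to differ. Outcomes {12} gives no origin for the 16 weeks; weeks of treatment is only implied by the sample size rationale.
- A reader might infer large variation between sites. The Recruitment section {15} describes pathology notification as a check that eligible patients are approached, and reports no delays.
- A reader might expect variation in the delay always to favour the claim. Concealed 1:1 allocation balances it in expectation, chance imbalance can go either way, and pure noise widens the interval, which makes non-inferiority harder to show.

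**Conclusion.** The point holds in a limited form. The protocol fixes a pre-allocation origin for a randomised primary comparison in which non-inferiority is claimed. Differences in time and Cox or log-rank results are untouched by an equal delay. Ratios of times shrink, for example from 1.33 to 1.26 or 1.21 with 2 or 4 weeks, under exponential remission and a hazard ratio of 0.75. A varying delay matters little for the hazard ratio at a mean of 2 weeks, slightly at 4, and materially only at about 8 (0.590 against 0.635, given a true value of 0.60 and exponentially distributed delays).

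All of these sizes rest on assumed delays. It would go too far to conclude that the non-inferiority claim is invalid: nothing in the document shows delays long enough for that. Where attenuation does occur with a truly slower reduced-dose arm, its direction favours the claim. This is a cheap improvement rather than a threat to the trial.

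**What to change.** Define the second primary endpoint as time from randomisation to remission, and state the same origin for the 16-week rate. Report the time from diagnosis to randomisation by arm as a baseline characteristic, together with any prednisolone given in that interval. Time from diagnosis can be kept as a descriptive or sensitivity analysis.

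The cost is a small protocol amendment, because a primary endpoint definition changes in an open-label trial that has been recruiting since 2018. It should be dated and made before outcomes are compared by arm. No new data should be needed, since randomisation is done electronically in RedCap. The sample size does not change, because it rests on the 16-week rate only.

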### Adverse event reporting and harms {22}

Subjective events during the trial will be reported by patients in questionnaires (SF36 and Cushing QoL). Local investigators will report adverse events after results of blood test (development of diabetes, infections, hyperlipidaemia), examinations (hypertension, weight gain, skin toxicity), and questionnaires (glucocorticoid toxicity index). All the events will be collected and stored in RedCap. In case of severe adverse events, the sponsor will be informed and report it to relevant authorities.

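### The persistent-hypercalcaemia safety endpoint depends on the response to lowering alfacalcidol, so it cannot be assessed as written in the control arm and omits cases that resolve on dose reduction

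*Protocol article*

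**What the plan says.** The safety list in Outcomes {12} includes persistent hypercalcaemia. It carries a duration of more than 2 weeks and is "defined by an elevated plasma-ionised-calcium and not normalising by reducing alfacalcidol dose".

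The arms differ in whether there is any alfacalcidol to reduce. Intervention description {11a} gives one arm "standard treatment with prednisolone 1 mg/kg/day" and the other "treatment with prednisolone 0.5 mg/kg/day combined with alfacalcidol 0.5 μg/day". The section on concomitant care {11d} closes the remaining route: "The patients cannot receive other immunosuppressants or active vitamin D during the trial".

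The criteria for modifying treatment {11b} say that the "alfacalcidol dose in the experimental arm may be reduced or discontinued if patients develop severe adverse events to these drugs", as judged by the local investigator. The same section states: "Examples of severe adverse events are hypercalcaemia due to alfacalcidol treatment". No duration or failure to normalise is required there.

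Two other provisions can pick up hypercalcaemia. One is the secondary endpoint in Outcomes {12}, "Rate of adverse events and number of hospital admissions". The other is in Adverse event reporting and harms {22}: "In case of severe adverse events, the sponsor will be informed and report it to relevant authorities".

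**The concern.** A safety endpoint in a randomised comparison should be something that any patient in either arm can be found to have or not have. Here the second condition asks how calcium responded to a change in a drug that one arm never takes. The text gives no rule for a control patient with raised calcium.

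In the experimental arm the condition selects cases by their response to a dose decision that is made after randomisation, by an unblinded investigator, and is possible in one arm only. A case that lasts more than 2 weeks and then resolves on reduction drops out of the endpoint. If alfacalcidol is stopped outright or left unchanged, the definition gives no clear answer either.

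The neighbouring safety item, severe adverse effects of prednisolone, carries no such condition, so it counts reversible harm. One of the trial's hypotheses (Objectives {7}) is that the reduced regimen lowers the incidence of adverse events. The background also says that active vitamin D has not been tested in this disease. A low count on this endpoint could be taken for tolerability when part of it comes from the definition.

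**Working it through.** The protocol states no hypercalcaemia rate, so there is no figure to reproduce. The check is a reading of the definition, followed by an illustration on assumed values.

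**Applying the definition case by case**

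| Patient with raised ionised calcium for more than 2 weeks | Counted under the stated definition? |
|---|---|
| Experimental arm, dose reduced, calcium stays high | Yes |
| Experimental arm, dose reduced, calcium normalises | No |
| Experimental arm, alfacalcidol stopped or left unchanged | Unclear |
| Control arm | Not assessable: no alfacalcidol dose to reduce |

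A definition by level and duration alone would count all four.

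**Size of the omission in the experimental arm**

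Inputs:
- n = 48 per arm, from 96 patients (Sample size {14}) allocated 1:1 (Sequence generation {16a}): 96 / 2 = 48.
- h = true proportion with hypercalcaemia lasting more than 2 weeks: assumed 5%, 10% or 20%.
- r = share of those that normalises on dose reduction: assumed 50% or 80%.

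Formulas:
- Expected cases by level and duration = 48 × h
- Expected cases under the stated definition = 48 × h × (1 − r)
- Chance that none is counted = (1 − h × (1 − r))^48

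For h = 10%:
- All cases: 48 × 0.10 = 4.8
- r = 50%: 4.8 × 0.5 = 2.4 counted; chance of none = 0.95^48 = 8.5%
- r = 80%: 4.8 × 0.2 = 0.96 counted; chance of none = 0.98^48 = 38%

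| h | Cases by level and duration | Counted, r = 50% | Counted, r = 80% | Chance of none, r = 80% |
|---|---|---|---|---|
| 5% | 2.4 | 1.2 | 0.48 | 62% |
| 10% | 4.8 | 2.4 | 0.96 | 38% |
| 20% | 9.6 | 4.8 | 1.92 | 14% |

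Whatever h is, the fraction missed equals r.

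**Effect of the control arm on the comparison**

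If the control arm were recorded as zero because the clause cannot be met, the apparent excess would grow. With h = 5%, an assumed control rate of 2% and r = 0, the level-and-duration excess is 5 − 2 = 3 points, while the endpoint would show 5 − 0 = 5 points. Only the exclusion of reversible cases lowers the apparent harm, so the two features of the definition pull in opposite directions.

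**The case against.** The best defence is that the item deliberately targets persistent, treatment-resistant hypercalcaemia, and that reversible cases are caught elsewhere. Section {11b} names alfacalcidol-related hypercalcaemia as a severe adverse event with no persistence condition, section {22} stores all events in the trial database and has severe ones reported, and the overall adverse event rate is a secondary endpoint. A drug-specific safety item also need not be comparable between arms, and the article states no formal test for it.

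Much of this stands, and it limits the point:

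- A reader might infer that the trial as a whole hides alfacalcidol harm. The documents do not support that, because these cases can still be recorded as adverse events. The backup is less specific, however: the blood-test examples in {22} do not mention hypercalcaemia, and no other endpoint names it.
- A reader might infer that the control-arm incidence is zero by definition. The text does not say how the clause applies without alfacalcidol, and an assessor could treat it as not applicable. Not assessable as written is the accurate description.
- A reader might infer that {11b} and {12} contradict each other. They set different thresholds for different purposes: one names events that may lead to a dose change, the other counts a narrower outcome.

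The defence does not justify the clause itself. The duration of more than 2 weeks already separates persistent from transient cases, and it can be applied in both arms. The extra condition adds only selection by response to alfacalcidol reduction.

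**Conclusion.** The point holds for this endpoint. As written it cannot be assessed in the control arm, and in the experimental arm it omits hypercalcaemia that lasted more than 2 weeks and resolved on dose reduction. The understatement equals the share that resolves. At an assumed true rate of 10% in 48 patients, 4.8 expected cases become 2.4 if half normalise and about 1 if 80% do.

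These counts rest on assumed rates, on 48 patients in the arm, and on every case having its dose reduced. The protocol gives neither the rate nor the share that resolves, so the figures show how the definition behaves and are not a forecast. A near-zero count is possible but not guaranteed. Hypercalcaemia is the only alfacalcidol harm that the protocol names; the protocol does not rank harms, so calling it the main added harm would go further than the text.

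**What to change.** In Outcomes {12}, delete the clause on response to alfacalcidol reduction. Define the endpoint as plasma ionised calcium above the reference range for more than 2 weeks. Count it in the same way in both arms, as randomised, and regardless of any change in alfacalcidol. Report alfacalcidol reduction or discontinuation for hypercalcaemia as a separate descriptive item. There is no need to widen the endpoint to any single raised value, since the duration criterion already keeps it to persistent cases.

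This changes measurement only and proposes no dosing rule. The cost is a change of wording, plus calcium results from blood samples in both arms. Whether the visit schedule already provides these cannot be judged, because the timeline figure is not shown. The reduced-dose arm's safety figure may look less favourable than under the present definition.
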